#### Patient and public involvement

Adults with SCI-related neuropathic pain living in the community were invited to share their perception of ‘priority research’ (in this case, treatments for neuropathic pain that are not pharmaceutical or invasive), feasibility and relevant outcomes (listed in this study), assessment, and study duration. They preferred remote interventions because many adults with SCI have transportation issues and some live in rural areas or out of state.

#### Who will take informed consent?

Eligible participants will have a virtual visit through the UMN secure Zoom conference ability with the study staff to review and address questions about the combined HIPAA/informed eConsent.

#### Additional consent provisions for collection and use of participant data and biological specimens

The eConsent will be signed through a UMN Research Electronic Data Capture (REDCap) link. REDCap uses a MySQL database via a secure web interface with data checks to ensure data quality during data entry. All IRB rules and HIPAA rules protecting the participants’ rights and confidentiality of records will be followed.

### Interventions

#### Explanation for the choice of comparators

Because this is the first study on Qigong in adults with SCI-related neuropathic pain, we decided on a quasi-experimental design and did not include a control group or a sham version of Qigong. We already have shown in a previous study with a similar group of adults with chronic SCI and similar neuropathic pain intensity levels, that neuropathic pain medication-only does not change the neuropathic pain intensity levels or any of the other SCI-related outcomes [25].

#### Intervention description: Qigong intervention

A Qigong Master from the Spring Forest Qigong™ Center (Minnesota) will teach the introductory class of the “Five Element Qigong Healing Movements” (6 h) over Zoom. These movements can be done lying or sitting, and thus, they are suitable for adults with SCI with paraplegia or tetraplegia [15, 21].

Additionally, [name] [name] developed specific kinesthetic imagery instructions to allow participants with all levels of mobility to participate maximally in the Qigong practice. The participants will be instructed to actively move however much they comfortably can and perform kinesthetic imagery. The instructions of the kinesthetic imagery are to focus on imagining the feeling of performing the entire whole-body movement standing up while focusing on breathing and body awareness and to imagine the ‘feeling’ of the contact of the floor with the soles of their feet and of the flow of the movements, rather than to ‘visualize’ the whole-body movement. If reproducing this feeling is difficult, participants will be asked to associate positive memories from before their SCI with this imagined standing posture, e.g., positive memories of feeling the warm sand under the soles of their feet on the beach or the feeling of grass under the soles of bare feet in the garden.

After the introductory class, participants will receive a password-protected website link to practice for 12 weeks.

*To address the feasibility outcome,* the Spring Forest Qigong^TM^ website automatically monitors the days and duration that videos are accessed, which allows us to objectively track adherence. The Spring Forest Qigong™ center will provide the weekly logs to the principal investigator. Since participants will log in with their ID code given at the start of the study, no personal information is transmitted to the website or the center.

#### Qigong practice

Qigong Master [name], MS in holistic healing, developed the video “Five Element Qigong Healing Movements”, and guides the participant on the online video through each of the five gentle horizontal and vertical arm and leg movements performed with guided breathing [13, 26]. As defined by Traditional Chinese Medicine, each of the five movements connects to a specific natural element (Fire, Earth, Metal, Water, and Wood). Each element is associated with two meridians, with a specific organ system, and with specific emotions, which have a positive and negative counterparts. When practicing the Five Element Qigong Healing Movements, the focus is directed only on positive emotions. The explanation of the five movements (Fig. 2) is detailed below [26].

**Fig. 2 Fig2:**
[figure not shown]
Depiction of the Five Element Qigong Healing Movements from Spring Forest Qigong™. *Legend:* The five movements are presented from left to right. Movement 1: Moving of Yin and Yang; Movement 2: Breathing of the Universe; Movement 3: Connecting with Heaven & Earth; Movement 4: Connecting with Your Body’s Energy; Movement 5: Connecting with Your Heart’s Energy. Details of how the different movements are performed are presented in the text

##### Preparation phase

The practice starts with smiling and focusing on the heart. The participants bounce for 1 min with their arms relaxed next to the body, and another minute with their arms in the air. [name] then guides the participants through various cupping and tapping movements to open the energy channels related to each of the five organ systems. The preparation phase ends with setting an intention for healing. Then the five movements are performed for 5 min each.

##### Movement 1: moving of Yin and Yang

This movement helps the liver system and is connected to the Wood element. The liver system is associated with the emotion of happiness (or its negative counterpart: anger). Movement 1 is performed by using the elbows to have the arms make an elliptical movement. The movement starts by moving the right hand out and down to the bottom of the torso, while the left hand moves in (closer to the body) and up to the face. While doing this movement, the focus is on the emotion of happiness and body sensations. After 5 min, the hands are brought down in front of the Lower Dantian, which is an energy center about the width of 3 thumbs below the navel and 3 thumbs inward. The participants focus on the Lower Dantian and take a deep breath three times.

##### Movement 2: breathing of the universe

This movement helps the heart system and is connected to the Fire element. The heart system is associated with the emotion of joy (or its negative counterpart: hatred). After Movement 1, on the fourth breath, the participants inhale, bend their knees, and open their hands to the sides. With the exhale, the hands come closer again and the participants straighten their body again. Participants focus on the emotion of joy and body sensations.

##### Movement 3: connecting with heaven and earth

This movement helps the stomach and spleen systems and is connected to the Earth element. The stomach and spleen systems are associated with the emotion of peace and groundedness (or its negative counterpart: anxiety and thinking). Movement 3 activates the triple heater, which is an energy system that helps the internal organs, glands, and lymph system. After Movement 2, the participants lower their hands to their sides and then move their hands up from both sides in the same way as they would hold a ball above their head. The hands are kept above the head during the entire duration of this movement. The participants inhale and bend their knees to lower the body slowly. As they exhale, they straighten their body. Participants focus on the emotion of peace and groundedness and body sensations.

##### Movement 4: connecting with your body’s energy

This movement helps the lung system and is connected to the Metal element. The lung system is associated with the emotion of contentment (and its negative counterpart: depression and sadness). Movement 4 directs energy to a point called Hui Yin at the center of the pelvic floor, 0.5 inch in front of the anus. This is where the female energy channels gather. Performing this movement is beneficial for the reproductive organs in women and prostate function in men. The participants bring both hands down and connect the tips of their fingers forming a heart shape in front of their navel. The participants keep a light pressure on the tips of their fingers to stimulate the heart’s energy. The participants bend the knees while keeping the spine and shoulders relaxed and straight and then spread the legs slightly by moving the right foot half a step out. While participants inhale, they shift the body weight to the left, putting 70% of the weight on the left leg and holding this position for three seconds. As they exhale, they switch the body weight and put 70% of the weight on the right leg. They hold this position for three seconds. The participants keep shifting their body weight in this way from side to side. During this movement, participants focus on the emotion of contentment and their body sensations.

##### Movement 5: connecting with your heart’s energy

This movement helps the kidney system and is connected to the Water element. The kidney system is associated with the emotion of gratitude and thankfulness (and its negative counterpart: fear). Movement 5 helps to move energy to the Bai Hui point on the top of the head. The participants adjust their feet, so they are standing with their feet shoulder-width apart. They put their hands together palm to palm in front of the chest while keeping a light pressure on the fingertips to stimulate the heart’s energy. During the inhalation, the participants slowly bend forward at the waist. This is a small movement. With the exhale, the participants straighten back up. While doing this movement the participants focus on the emotion of gratitude and body sensations.

##### The ending: harvesting of Qi

The participants rub the hands together, palm to palm, and then massage the face and ears, comb through the hair, followed by cupping and tapping parts of the body. They then make gentle dolphin movements with the neck and body, and after more cupping, the practice ends by lifting and dropping the heels nine times.

#### Criteria for discontinuing or modifying allocated interventions

The risks of Qigong practice are minimal and expected to be limited to mild transient discomfort. Stopping rules and subsequent removal from the study will be applied when a participant is found to be intolerant to the required study procedure at any time point; serious adverse events at any time point; develops an intercurrent illness that would, in the judgment of the principal investigator, affect the assessment of clinical status to a significant degree; or requests to withdraw from the study. Serious adverse events will be reported as per IRB and Good Clinical Practice requirements. In sum, because of the low-intensity Qigong movements or kinesthetic imagery, we anticipate that this trial will be safe and well-tolerated. Thus, we do not anticipate terminating the trial due to safety or tolerability issues.

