## Methods: participants, intervention, and outcomes

### Trial design

The study flow chart of this quasi-experimental pre-post design is presented in Fig. 1. Participants with SCI-related neuropathic pain and with complete or incomplete paraplegia or tetraplegia will perform 12 weeks of “Five Element Qigong Healing Movements” of Spring Forest Qigong™ with an online video at home, at least 3 × /week, 41 min/session. *Individual weekly check-ins* (15–30 min) are organized during the Qigong practice to address questions and demonstrate movements over Zoom if needed. Qualitative information will be collected about their adherence, adverse outcomes if any, perceptions, effects, and satisfaction with the Qigong practice. During the whole study period, we will record weekly the highest, average, and lowest neuropathic pain intensity ratings perceived in the prior week, the dose of neuropathic pain medication, recent illnesses, health care utilization, and/or recent hospitalizations, and any activity that would indicate community integration.

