#### Plans to promote participant retention and complete follow-up

Participants will be encouraged to complete all scheduled virtual visits and assessments. Given that this study is starting during the COVID-19 pandemic, we estimate 90% adherence and 30% attrition given a high likelihood of some participants being exposed to COVID-19 during the study. If an assessment or weekly check-in is missed, care will be taken to get the information at a later time. There are no stop criteria for missed sessions or testing. The study team will decide when to consider a participant “lost to follow-up” based on clinical/scientific judgment on a case-by-case basis. Missed testing sessions will be recorded for consideration during the analysis but will not be cause for removal from the study.

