### Statistical methods

#### Sample size

To our knowledge, this will be the first study evaluating the feasibility of Qigong on neuropathic pain perception. This study will also provide preliminary estimates of effect size, crucial to generate hypotheses for future larger randomized controlled trials. We will recruit a total sample size of 18 participants. This is based on our estimated accrual rates. With the sample size, we will be able to estimate the rate parameters of our feasibility endpoints between 70 and 90% to be within 95% confidence intervals of ± 21% and ± 14% respectively. Based on data from another body awareness therapy in adults with SCI [25], the sample size will also lead to 95% confidence intervals for pain estimates of ± 0.5.

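### The rule for intolerance, serious adverse events and qualifying illness ends study participation, not only practice, so later pain and safety data are lost selectively

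*Protocol article*

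**What the plan says.** The rule is in the protocol article under *Criteria for discontinuing or modifying allocated interventions*: "Stopping rules and subsequent removal from the study will be applied when a participant is found to be intolerant to the required study procedure". The other triggers are "serious adverse events at any time point", a participant who "develops an intercurrent illness that would, in the judgment of the principal investigator, affect the assessment of clinical status to a significant degree", and a participant's own request to leave. The same section adds: "Serious adverse events will be reported as per IRB and Good Clinical Practice requirements".

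Other sections bear on it:

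- *Plans to promote participant retention and complete follow-up* sets no stop criteria for missed sessions and says: "Missed testing sessions will be recorded for consideration during the analysis but will not be cause for removal from the study". It also states that "we estimate 90% adherence and 30% attrition", giving COVID-19 exposure as the reason.
- *Trial design* and *Objectives* plan six weeks of assessment without practice after week 12, then practice at will up to the 1-year assessment. *Trial design* also has the team record weekly "recent illnesses, health care utilization, and/or recent hospitalizations".
- The feasibility table under *Outcomes* counts withdrawals with their reasons and counts adverse events. It asks about satisfaction at week 12 and at both follow-ups.
- *Sample size*: "We will recruit a total sample size of 18 participants". There is no comparator.
- The section on non-adherence and missing data names multiple imputation and inverse probability weighting.

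**The concern.** The section's heading is about the intervention, but the consequence it states is at the level of the study. Nothing in the article separates stopping practice from leaving the study, and nothing provides for assessments after a removal.

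The participants affected are selected by tolerability, safety or illness. Whether Qigong is well tolerated is one of the study's questions, and the results are to inform the decision on a larger randomised trial. Without a control group, selective loss goes straight into the before-after pain estimate. The course after a serious event is not followed within the study, and someone removed before week 12 may never be asked about satisfaction.

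**Working it through.** **1. The passages side by side**

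| Situation | What the article provides |
|---|---|
| Misses sessions or testing | Stays in the study |
| Weeks 12 to 18, no practice | Everyone continues to be assessed |
| Up to 1 year, practice at will | Everyone is assessed again |
| Intolerant to the study procedure | Removed from the study |
| Serious adverse event, any time, related or not | Removed from the study; event reported |
| Illness judged to affect clinical assessment | Removed from the study |

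Follow-up of people who are not practising is therefore already planned. It is closed only to those who meet a tolerability, safety or illness trigger. In the six weeks without practice there is no assigned practice to stop, so the rule's only effect there is to end data collection.

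**2. What is kept and what is lost**

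Kept: the triggering event, the reason for withdrawal, and everything collected before removal, since no section discards it. Lost: later pain ratings, later questionnaires, and the course after the event.

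**3. The plan's own precision, as a yardstick**

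*Sample size* gives half-widths of 21 and 14 percentage points for rates of 70% and 90%. With n = 18:

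- 1.96 × √(0.70 × 0.30 / 18) = 0.212
- 1.96 × √(0.90 × 0.10 / 18) = 0.139

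Both match, and both use all 18 participants. The pain half-width of 0.5 cannot be reproduced because no SD is given. It implies an SD of 0.5 × √18 / 1.96 = 1.08, or about 1.0 with the t distribution.

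**4. Size of the possible bias (assumed inputs)**

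Let k of 18 be removed, let m be the mean pain change of those kept, and let the removed do D points worse on average.

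- Mean of all who started: [(18 − k) × m + k × (m + D)] / 18 = m + D × k / 18
- Mean of those kept: m
- Difference: D × k / 18

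Example with m = −1.0, k = 3, D = 1: (15 × (−1) + 3 × 0) / 18 = −0.83, against −1.0 in those kept. The difference is 0.17.

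| k removed | D = 1 | D = 2 | D = 3 |
|---|---|---|---|
| 2 | 0.11 | 0.22 | 0.33 |
| 3 | 0.17 | 0.33 | 0.50 |
| 5 | 0.28 | 0.56 | 0.83 |

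Most cells lie below the stated half-width of 0.5. It is reached at k = 3 with D = 3 and passed at k = 5 with D = 2 or more. Five of 18 (28%) is close to the article's 30% attrition, but the article ties that figure to COVID-19, so it is not a forecast of removals under this rule.

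**5. What the missing-data methods can do**

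If imputation or weighting recovers a share r of the difference, (1 − r) × D × k / 18 remains. In standard form both methods assume that observed data explain the loss. Baseline and weekly ratings up to removal help. With 18 participants and a handful of removals, there is little from which to model either the loss or the outcome after it.

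**The case against.** The strongest reply is that this is a descriptive single-group pilot whose results are to be validated in a larger controlled study. The article is condensed and, for serious adverse events, defers to an IRB plan that is not shown and may provide for follow-up after an event. Multiple imputation and weighting are named, so an analysis of completers alone is not what is planned. In a feasibility study, removal for intolerance properly counts against retention, and the reasons are recorded.

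Much of this stands and limits the point. Several stronger readings that a reader might infer are not supported:

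- *The worst cases vanish from the safety data.* They do not. The event is reported and the withdrawal and its reason are counted; only later follow-up is lost.
- *Any illness leads to removal.* The rule requires the investigator's judgment that the illness affects clinical assessment.
- *The weekly recording of illness and hospitalisation contradicts the rule.* An entry can be made and follow-up then end. The article does not define seriousness, so a count of removals built on an assumed hospitalisation rate has no basis in it.
- *The pain effect will be overstated by a known percentage.* That needs invented outcomes for those removed and a completers-only analysis. A serious event unrelated to Qigong need not mean worse pain; the inference is strongest for intolerance.

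The reply does not dispose of the rule itself. Removal from the study is stated in the text, not left out by condensation, and deferring serious events to the IRB plan does not cover intolerance or illness.

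**Conclusion.** The point holds as a design weakness of moderate weight. Followed as written, the rule ends data collection for people selected by tolerability, safety or illness, in a single group of 18 where tolerability is an objective. The before-after pain estimate can be biased as a result. The illustration gives 0.17 points for 3 removals who do 1 point worse, and 0.11 to 0.83 points across 2 to 5 removals and differences of 1 to 3 points. The number removed, their outcomes and the analysis of those kept are all assumptions; the documents give none of them. The planned methods would reduce the bias by an unknown share. No position is taken on which events should stop practice.

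**What to change.** Leave the criteria for stopping Qigong practice unchanged. Replace the consequence of removal from the study with wording such as: *When a criterion is met, the remaining scheduled pain ratings, outcome assessments and adverse-event check-ins continue unless the participant withdraws consent.*

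Then:

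- include everyone who started in the analysis;
- report stops of practice separately from withdrawals from the study, each with its reason;
- align the discontinuation section with the retention section, which already keeps participants who miss sessions or testing, and check that the IRB procedure for serious events says the same.

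The cost is a short amendment, a change to the consent wording, and a few more questionnaires from people who have stopped practising. Assessments are remote and already scheduled, so no new visits are needed.

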#### Strategies to improve adherence to interventions

We will organize weekly phone calls to address questions about the Qigong practice and demonstrate movements over Zoom if needed. Qualitative information will be collected about their adherence, adverse outcomes if any, perceptions, effects, and satisfaction with the Qigong practice.

#### Relevant concomitant care permitted or prohibited during the trial

Concurrent practice of other mind–body approaches is not permitted. Their regular standard-of-care (any medication intake) as well as health care appointments will be maintained to ensure adequate care for other SCI-related symptoms, but appointments for neuropathic pain (e.g., osteopathy) will not be scheduled or permitted during the study.

#### Provisions for post-trial care

All assessments and practice are delivered remotely. The study does not provide compensation for research-related injuries or unexpected urgent care.

### Outcomes

#### Feasibility benchmarks

Our feasibility markers are consistent with models and guidelines for intervention development [27, 28]. Based on prior publications [29–32], we will assess the following *a-priori* feasibility markers.

**Table Taba:** 

Feasibility item and details	Benchmark
*Recruitment/enrollment* ◦ Assess recruitment rates (screens and enrollment, sex/racial outcomes) ◦ Evaluate the recruitment rate for complete and incomplete SCI	◦ The proportion of potential participants contacted who agreed to participate: 80% is excellent and 70% good ◦ Ratio of complete/incomplete SCI. We estimate recruitment of 30–40% of adults with complete, 60–70% with incomplete SCI ◦ Reasons for (not) participating will help delineate facilitators and barriers to participation
*Feasibility and acceptability of the study design* ◦ Drop-out rates	◦ Proportion of people withdrawing from the study and the reason for withdrawing. A proportion of 90% staying in the study is excellent, 80% good (i.e., 20% drop-out)
*Feasibility, adherence, and acceptability of the Qigong practice* ◦ Assess intervention adherence, average Qigong practice; at least 3×/week (123 min)	◦ Weekly/monthly check-ins (reporting min/week of practice) to monitor adherence. The Spring Forest Qigong^TM ^website also logs the day, time, and duration of video access ◦ Feasibility: Excellent: > 80% participants practice at least 2 × /week; good ≥ 70% ◦ Drop-out due to lack of interest will be counted as general attrition: 10% drop-out is excellent, 20% is good
*Feasibility of adhering to the collection of quantitative measures* ◦ % Adherence in completing all assessments during the study (until 6 weeks follow-up) ◦ % adherence for the 1-year post-intervention assessments	◦ Feasibility is ‘excellent’ when none of the questionnaires are fully missing in > 25% of the participants
*Program satisfaction* ◦ interview about satisfaction with the Qigong practice, and the study	◦ Excellent satisfaction: ≥ 75% of participants report being satisfied with the study and Qigong practice; and good if ≥ 70% of participants are satisfied. We will ask them about satisfaction at the end of the 12 weeks of practice and at the end of the 6-week, and 1-year follow-up
*Program safety* ◦ Assess adverse events (IRB + Good Clinical Practice reporting guidelines)	◦ Excellent safety: no study-related adverse events; good if there are minimal and mild adverse events (e.g., muscle soreness) linked to Qigong practice in max 10% of participants. We will ask about adverse events on our weekly and monthly check-in calls

We will collect patient-centered outcome measures on neuropathic pain intensity and symptoms associated with pain.

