### Objectives

In this quasi-experimental study, we will test our hypothesis that the remotely delivered Qigong will reduce SCI-related neuropathic pain by improving body awareness. If our hypothesis is validated, the outcome of our work will be the first step in demonstrating a potentially effective therapy for adults with SCI-related neuropathic pain. To test this hypothesis, we will determine whether 12 weeks of remote Qigong is *feasible and well-tolerated* and whether it reduces neuropathic pain in adults with SCI. Given the reported associations with pain, we will assess whether Qigong practice reduces spasms frequency and/or severity, and improves function, mood, and body awareness. The feasibility of the 6-week follow-up will investigate how long potential Qigong effects remain without practicing. After the 6 weeks, participants can resume practice at will. The feasibility of the 1-year follow-up will examine possible behavioral changes of participants in practicing Qigong in their daily life.

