### Participant timeline

Table 1 displays the scheduling of assessments and timeline of each study section.

**Table 1 Tab1:** Scheduling of enrolment, intervention, and assessments

	Study period				
	Enrolment + Baseline assessment	Intervention + assessments		6-week Follow-up period (no intervention)	1-year Follow-up period (practice at will) + close-out
Timepoint	*Week 0*	*Week 6*	*Week 12*	*Week 18*	*1-year*
Enrolment:					
Eligibility screen	X				
eConsent	X				
Intervention:					
*Qigong practice for 12 weeks, at least 3* × */week*		X	X		X
Assessments:					
*Demographic and general health data*	X				
Weekly assessment of the highest, average, and lowest neuropathic pain intensity levels in the prior week	X	X (weekly)	X (weekly)	X (weekly)	X
* Other outcome assessments*	X	X	X	X	X

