#### Statistical methods

Rate parameters for the feasibility markers will be estimated based on the participants who achieved each benchmark, with 95% confidence intervals constructed based on exact binomial confidence interval. The continuous measures of feasibility will be summarized using descriptive statistics with 90% confidence intervals constructed. The occurrence of protocol deviation or non-adherence will be summarized and tabulated using frequency tables. The reasons of protocol deviation or non-adherence will be documented and investigated for improved clinical design in future large studies.

All quantitative variables will be summarized using descriptive statistics for all subjects as well as each group at each time point. For longitudinal outcomes, across-time changes and correlations will also be estimated for all participants as well as each group that will be used for sample size determination in future studies. All analyses will be done using standard statistical software including SAS, Stata, and R. The data analysis from this quasi-experimental study will provide an estimate of key trial elements to determine whether to proceed to a larger definitive randomized controlled trial.

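### Adherence is graded on practising at least twice a week although the regimen is at least three times a week, so the grade alone cannot show that the prescribed regimen is feasible

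*Protocol article*

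**What the plan says.** The regimen is the same wherever the protocol article states it. Under Trial design, participants practise "with an online video at home, at least 3 × /week, 41 min/session". Table 1 under Participant timeline has "Qigong practice for 12 weeks, at least 3" times a week, and the abstract gives the same frequency.

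The adherence row of the table under Feasibility benchmarks uses two frequencies:

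- The item column says "Assess intervention adherence, average Qigong practice; at least" three times a week, with 123 min in brackets.
- The benchmark column calls feasibility excellent when more than 80% of "participants practice at least 2 × /week", and good at 70% or more.

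The text above the table describes the markers as a-priori, drawn from prior publications, and adds: "Our feasibility markers are consistent with models and guidelines for intervention development". The article gives no reason for the lower frequency and does not call it a minimum acceptable dose.

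On analysis, the Statistical methods section says: "Rate parameters for the feasibility markers will be estimated based on the participants who achieved each benchmark", with exact binomial 95% intervals. It also plans descriptive summaries of continuous feasibility measures with 90% intervals, and frequency tables of protocol deviation or non-adherence. The results are meant to help decide whether a larger randomised trial should follow.

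**The concern.** The row names one quantity and grades another. A person who practises exactly twice a week throughout falls short of the regimen but counts as a success in the graded proportion. No benchmark is set for the share who reach three sessions a week, and the article does not commit to reporting that share.

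Under Objectives the article says "we will determine whether 12 weeks of remote Qigong is" feasible and well tolerated, and the intervention it defines is three sessions a week. A reader who sees adherence graded excellent may take it that participants managed that dose. If a definitive trial is then designed at three sessions a week on the strength of the grade, its assumed adherence will not have been estimated at that dose.

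**Working it through.** **Inputs from the protocol article**

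- Session length 41 min, at least 3 sessions a week, 12 weeks (Trial design). The abstract mentions a 45-min video; 41 min is used here because it reproduces the table's figure.
- Adherence item: at least 3 a week, 123 min. Benchmark: at least 2 a week, excellent above 80%, good at 70% or more (Feasibility benchmarks table).
- n = 18 (Sample size). All 18 are assumed to be in the denominator.

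**The plan's own dose figure.** 3 × 41 = 123 min a week, as printed. The item column therefore refers to the prescribed regimen.

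**Dose at the graded threshold.** 2 × 41 = 82 min a week, and 82/123 = 67%. Over 12 weeks this is 24 sessions against 36.

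**Counts needed for each grade**

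- Excellent: 0.80 × 18 = 14.4, so at least 15 people.
- Good: 0.70 × 18 = 12.6, so at least 13 people.

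**What a grade implies about the regimen.** Everyone at 3 or more a week is also at 2 or more. If x people meet the benchmark, the number on the regimen can be anything from 0 to x. Exact (Clopper-Pearson) 95% intervals:

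| Observed at ≥2/week | Grade | Possible number at ≥3/week |
|---|---|---|
| 15/18 = 83.3% (58.6–96.4%) | Excellent | 0/18 = 0% (0–18.5%) up to 15/18 = 83.3% (58.6–96.4%) |
| 13/18 = 72.2% (46.5–90.3%) | Good | 0/18 = 0% (0–18.5%) up to 13/18 = 72.2% (46.5–90.3%) |

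**Chance of each grade under assumed true rates.** These are binomial tail probabilities with n = 18.

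- If 90% truly reach 2 a week, P(15 or more) = 0.90, whatever share reaches 3 a week.
- Suppose only 50% truly reach 3 a week. On a three-a-week count, P(13 or more) = 0.048 and P(15 or more) = 0.004.

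Both rates can hold in the same population, so the same participants would very probably be graded excellent on the planned count and very probably miss even good on a count against the regimen.

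**Would the planned average reveal it?** Not necessarily. Take an assumed split of 6 people at 5 sessions a week (205 min) and 12 at 2 (82 min):

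- Mean = (6 × 205 + 12 × 82)/18 = (1230 + 984)/18 = 123.0 min, exactly the stated target.
- Benchmark: 18/18 at 2 or more, graded excellent.
- Regimen: 6/18 = 33.3% (13.3–59.0%) at 3 or more.

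**The case against.** The strongest reply is that the two frequencies do different jobs: one is the dose prescribed, the other the minimum graded. Grading adherence below the full dose is not an error in itself. The markers are described as a-priori and rest on sources that cannot be seen here, so the lack of a rationale in a condensed article proves little. This stands, and it is why the benchmark should be kept. Those sources could justify twice weekly as a threshold, but they cannot turn a twice-weekly proportion into a measure of adherence to three sessions a week.

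A second reply is that practice against three a week will be visible anyway. Average practice is named in the row, minutes and log data are collected, and non-adherence will be tabulated. Three a week is the only frequency prescribed, so non-adherence is most naturally counted against it. If nobody reached three sessions a week, average practice would fall below 123 min (at 41 min a session). In the split shown above, the median would be 82 min and the SD about 60 min, which would alert a careful reader. Much of this stands, and it limits the severity. It does not close the gap: a mean, median and SD do not give the share on the regimen, and the article does not say which frequency defines non-adherence while its own adherence row contains two.

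A third reply is that the article never says this grade alone will decide feasibility. It spreads feasibility over recruitment, retention, practice, data completeness, satisfaction and safety, and says the data will inform dosage in later trials. That is correct. The point is therefore about what the adherence grade can support, not about the whole feasibility assessment.

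Finally, an extra descriptive proportion might be left to a fuller document. But the item, the threshold and the bands are all fixed in this article, and the mismatch is between them.

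**Conclusion.** The concern holds. The only graded practice-frequency proportion is set at two sessions a week, 67% of the prescribed minimum, and it does not measure adherence to the regimen the trial prescribes. With 18 participants, an excellent grade at 15/18 leaves the share on the regimen anywhere between 0% and 83%. That range is a logical bound, not a prediction. The 6-and-12 split and the assumed true rates of 90% and 50% are illustrations. A smaller analysed number would change the counts but not the argument.

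The consequence is minor to moderate. It limits what can be concluded about three sessions a week and should be fixed, but it does not invalidate the twice-weekly benchmark or the trial. Confidence is medium, because the sources cited for the markers and any fuller protocol or analysis plan are not at hand.

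**What to change.** 1. Keep the twice-weekly benchmark and its bands, and label it as minimum acceptable adherence.
2. Report beside it the proportion practising at least three times a week with its exact 95% interval, counted in the same way and on the same denominator.
3. Present that figure descriptively, without new pass/fail bands, and disclose that it was added after recruitment began on July 1, 2021 (Trial status).
4. Rest any statement that the three-times-weekly regimen is feasible on that proportion.

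The cost is one extra proportion and one label. No new data collection is needed, since the Spring Forest Qigong "website automatically monitors the days and duration that videos are accessed, which allows us to objectively track adherence". Sample size and trial conduct do not change. The adherence conclusion may look less favourable, and the added figure cannot be presented as a-priori.
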